# Efficacy of night-time compression for breast cancer related lymphedema (LYNC): protocol for a multi-centre, randomized controlled efficacy trial

**DOI:** 10.1186/s12885-016-2648-8

**Published:** 2016-08-04

**Keywords:** Breast cancer, Lymphedema, Compression therapy, Physical therapy

## Abstract

**Background:**

Lymphedema is a prevalent long-term effect of breast cancer treatment that is associated with reduced quality of life. More recent observational data suggest that the addition of night-time compression to day-time use of a compression garment results in better long-term control of arm lymphedema. The primary objectives of the randomized controlled phase of the trial are to determine the efficacy of night-time compression on arm lymphedema volume maintenance and quality of life in breast cancer survivors who have completed intensive reduction treatment for their lymphedema.

**Methods/Design:**

The study will be a parallel 3-arm, multi-centre randomized fast-track trial. A total of 120 women with breast cancer related lymphedema will be recruited from 3 centres in Canada and randomized to group 1: Day-time compression garment alone or Group 2: Day-time compression garment + night-time compression bandaging or Group 3: Day-time compression garment + use of a night-time compression system garment. The duration of the primary intervention period will be 12 weeks. The follow-up period after the intervention (weeks 13 to 24) will follow a longitudinal observational design. The primary outcome variables: differences from baseline to week 12 in arm volume and quality of life (Lymphoedema Functioning, Disability and Health Questionnaire: Lymph-ICF). Secondary outcomes include bioimpedance analysis, sleep disturbance and self-efficacy. All measurements are standardized and will be performed prior to randomization, and at weeks 6, 12, 18 and 24.

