### Objectives

The primary objectives of the randomized controlled phase of the trial are to determine the effect of night-time compression on arm lymphedema volume maintenance and quality of life in breast cancer survivors who have completed intensive reduction treatment for their lymphedema. These questions are seen as valuable for informing implementation of night-time compression as a self-management strategy for lymphedema in the clinical setting. The primary objectives of follow-up are to evaluate the long-term adherence to use of night-time compression and the timing of the intervention effect. As well, this follow-up period will allow us to better understand who may benefit the most (or least) from the addition of night-time compression.

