### Primary endpoints

*Arm volume* is a commonly used metric to evaluate lymphedema severity and to inform decision-making in the clinical setting. Lymphedema will be objectively measured using the Perometer (Pero-systems, Wipputal, Germany). The Perometer is an optoelectric limb volumeter that uses infrared technology to quantify limb volume and determine inter-limb difference. Measurement with the perometer takes approximately 3 min to complete. The perometer is a valid, reliable, and sensitive method for quantifying limb volume [16–18].

*Quality of life* will be measured using the condition-specific Lymphoedema Functioning, Disability and Health Questionnaire (Lymph-ICF) [19]. This 29-item questionnaire was developed to assess quality of life specific to lymphedema and to monitor progress of treatment on function (i.e., movement, activities) and symptoms related to lymphedema (i.e., pain, discomfort, heaviness, and tension) as well as to assess activity limitations and participation restrictions. The Lymph-ICF has been tested and shown to be valid and reliable [19]. As well, general health-related quality of life will be assessed at each visit by using the RAND 36-item Short Form Health Survey (SF-36). These two questionnaires will take approximately 10–15 min to complete.

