### Sample size for randomized fast-track trial phase

The sample size required per group to detect at least a minimal clinically important mean difference of 20 % (SD ±25) in arm lymphedema volume in favor of either the standard care + NCSG, standard care + CB group and standard care alone is 36 participants. A total sample of 108 participants will achieve a power of 86 % with a significance level of 0.05 using a one way ANOVA test. The sample size required per group to detect at least a minimal clinically important difference on the Lymph-ICF quality of life scale of 15 points out of 100 (SD ±22) between the standard care + CB group and the standard care + NCSG group is 36 participants. A total sample of 108 will achieve a power of 80 % with a significance level of 0.05 using a two-sided Mann-Whitney test assuming the actual distribution is normal. To allow for an estimated 10 % loss to follow-up and non-compliance/cross-over of the standard care group, we will recruit an additional 12 patients for a total of 120 participants (40 participants in each of the three treatment groups).

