### Statistical analyses

Baseline medical and demographic characteristics, arm dominance relative to the lymphadematous arm, and adverse events of the three groups will be compared using one-way ANOVA for continuous data and Pearson’s Chi-square tests for categorical data. The primary analysis will compare the groups with regard to percent excess lymphedema volume and quality of life at 12-weeks using a one-way ANOVA. General linear models will be used to adjust for centre and lymphedema category (mild or moderate), and to evaluate the treatment effect in subgroups defined by the strata. Sleep quality, self-efficacy, and adherence-related outcomes will be analyzed by repeated measures modeling and one-way ANOVA on change scores.

Descriptive data on accrual rates will include the number of women screened for eligibility, the number eligible, the number agreeing to participate, and reasons for refusal to participate. Data on adherence will be collected from all women throughout the 24-week study period. Adherence data will include days worn per week and hours worn per 24-h period, as appropriate, for each of the following: 1) NCSG; 2) CB; 3) day-time compression sleeve. We will also examine adherence during weeks 13 to 24 to the newly assigned NCSG for the standard care and standard care + CB groups, and ongoing adherence during weeks 13 to 24 in the originally assigned standard care + NCSG group. Analyses of primary outcomes will be performed at the end of the RCT portion of the trial. Within group analyses will also be conducted for primary and secondary outcomes from weeks 13 to 24 following completion of all follow-up measures.

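### Arm volume and Lymph-ICF are unranked primary outcomes, each sized at the full 0.05 with no success rule: familywise error is about 8–10% if either counts, and the stated powers do not describe the trial if both must succeed

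*Protocol article*

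**What the plan says.** The Abstract (Methods/Design) lists the primary outcomes together: "The primary outcome variables: differences from baseline to week 12 in arm volume and quality of life". It identifies the quality-of-life instrument as the Lymph-ICF. The Objectives section is equally unranked; the aim is to "determine the effect of night-time compression on arm lymphedema volume maintenance and quality of life in breast cancer survivors".

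The section on sample size for the randomized phase makes two separate calculations, each arriving at 36 per group:

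- **Arm volume:** a "minimal clinically important mean difference of 20 % (SD ±25) in arm lymphedema volume", tested "with a significance level of 0.05 using a one way ANOVA test". It states: "A total sample of 108 participants will achieve a power of 86" per cent.
- **Lymph-ICF:** a 15-point difference (SD 22) between the bandaging (CB) and night-time garment (NCSG) groups, at 80% power "with a significance level of 0.05 using a two-sided Mann-Whitney test".

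The Statistical analyses section then treats both as one primary analysis: "The primary analysis will compare the groups with regard to percent excess lymphedema volume and quality of life at 12-weeks using a one-way ANOVA". None of these sections gives an order of testing, a division of alpha, or a statement that one or both outcomes must be significant.

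**The concern.** Two tests, each at 0.05 and each able to yield a primary claim, do not together have a 0.05 error rate. Requiring both to succeed controls the error, but the chance of success is then the joint power, which is below both 86% and 80%. The article does not say which rule applies, so its significance level and its powers cannot all describe the same confirmatory claim.

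At stake is how a mixed result is read. If one outcome is significant and the other is not, the text lets the trial be called positive or negative after the fact. Lymph-ICF is also self-reported, by women who know their treatment (Blinding section).

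**Working it through.** **Inputs.** From the sample size section: 36 per group; arm-volume difference 20, SD 25, alpha 0.05, power 86%; Lymph-ICF difference 15, SD 22, two-sided alpha 0.05, power 80%. Not given and therefore assumed: the correlation between the outcomes (0 to 0.7) and the pattern of the three arm-volume means.

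**1. Reproducing the stated powers**

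- Arm volume, one-way ANOVA with means 0/10/20: noncentrality λ = 36 × (10² + 0² + 10²) / 25² = 11.52. With 2 and 105 degrees of freedom the power is 85.9% (stated: 86%).
- Lymph-ICF, Mann-Whitney under normality: effective n = 36 × 0.955 = 34.4 per group. Noncentrality = 15 / (22 × √(2/34.4)) = 2.83, giving 79.6% by noncentral t, or 80.7% by the normal approximation (stated: 80%).

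Both figures reproduce, and both use the whole 0.05.

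**2. Either outcome suffices**

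Independent outcomes: 1 − 0.95² = 9.75%. For correlated outcomes, from the bivariate normal with two-sided 0.05 limits:

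| Correlation | Familywise error |
|---|---|
| 0 | 9.75% |
| 0.3 | 9.5% |
| 0.5 | 9.1% |
| 0.7 | 8.3% |

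A simulation of 20,000 trials with three groups of 36 and an F test on each outcome gave 10.0%, 9.2%, 9.1% and 8.6%. The simulation standard error is about √(0.095 × 0.905 / 20,000) = 0.2 percentage points. This counts one test per outcome; pairwise comparisons among the three groups are not included.

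**3. Both outcomes required**

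Independent: 0.86 × 0.80 = 68.8%. If both night-time groups gain 20 points (means 0/20/20), λ = 36 × (13.33² + 6.67² + 6.67²) / 25² = 15.36 and arm-volume power is 94.3%, so the product is 0.943 × 0.80 = 75.4%. With correlated test statistics:

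| Correlation | Joint power, 86% and 80% | Joint power, 94.3% and 80% |
|---|---|---|
| 0 | 68.8% | 75.4% |
| 0.3 | 70.9% | 76.6% |
| 0.5 | 72.7% | 77.6% |
| 0.7 | 74.9% | 78.7% |

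**4. Power under error-controlling rules (36 per group, means 0/10/20)**

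- *Equal split, 0.025 each:* arm volume 78.5%, Lymph-ICF 70.3%.
- *Holm, assuming independence:* an outcome is claimed if its own p-value is at most 0.025, or lies between 0.025 and 0.05 while the other is at most 0.025.
  - Arm volume: 0.785 + (0.859 − 0.785) × 0.703 = 0.837.
  - Lymph-ICF: 0.703 + (0.796 − 0.703) × 0.785 = 0.776.
- *Fixed sequence, arm volume first:* arm volume keeps 86%. Lymph-ICF can be claimed only if both tests succeed, so its power is the joint power: 69–73% for correlations 0 to 0.5, and 75% at 0.7.

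**5. Sensitivity to the Lymph-ICF test**

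Lymph-ICF is sized by a two-group Mann-Whitney test but analysed by three-group ANOVA. With the F test, its power at 0.05 is 72.5% (means 0/7.5/15) or 84.7% (0/0/15); at 0.025 it is 62.2% or 76.9%. Its Holm power is then 0.622 + (0.725 − 0.622) × 0.785 = 0.703, or 0.769 + (0.847 − 0.769) × 0.785 = 0.830.

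**The case against.** The strongest reply is that a success rule is normally left to the full protocol or the SAP, neither of which is shown, and that the two values of 0.05 are only planning inputs. The first part is fair: absence of a rule from an article is not in itself an error. What remains is that the article fixes the full 0.05 for each outcome and derives its sample size and powers from it. A rule held elsewhere that controls the error across both outcomes, whether a split, Holm, a fixed sequence or joint success, would leave at least one stated power too high for the confirmatory claim.

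A second reply is that the outcomes answer separate questions. The Hypotheses section ties arm volume to each night-time method against standard care, and quality of life to NCSG against both other groups. Whether distinct questions must share alpha is partly a matter of judgement. But the Objectives and Statistical analyses sections place them in one primary family, and the article does not say that they are to be judged separately.

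Three stronger readings are tempting and are not supported:

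- *Night-time compression could be declared effective on the questionnaire alone.* Lymph-ICF is powered for CB against NCSG, both of which are night-time compression. A difference there would favour one method over the other, not establish that night-time compression works.
- *SF-36 opens a third route to a primary claim.* It does appear under Primary endpoints: "As well, general health-related quality of life will be assessed at each visit by using the RAND 36-item Short Form Health Survey (SF-36"). But the Abstract and the sample size section both name Lymph-ICF as the primary quality-of-life instrument, so this is untidy placement only.
- *Joint power is simply about 70%.* That figure depends on arm-volume means of 0/10/20 and on a Mann-Whitney test that the analysis section does not use.

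**Conclusion.** The point holds. As written, the 0.05 level applies to each primary outcome but not to the pair. If either may carry a primary claim, the familywise error is 9.75% under independence, 9.1% at correlation 0.5 and 8.3% at 0.7. If both are required, the error is controlled but joint power is 69–75% on the stated figures, or about 75–79% if both night-time groups gain 20 points on arm volume.

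The error figures rest on one test per outcome and an assumed correlation. The joint powers rest also on the stated 80% for Lymph-ICF, which belongs to the sizing test and not to the planned ANOVA. The document does not show which rule the investigators intend, so neither consequence can be called the trial's actual operating characteristic. This should be corrected; it does not undermine the design or the size of the trial.

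**What to change.** Before any outcome analysis, state whether one or both primary outcomes define success, and control the error across the two. Options:

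1. **Holm over the arm-volume and Lymph-ICF F tests (preferred).** It needs no ranking. At 36 per group it keeps about 84% for arm volume and 78% for Lymph-ICF, using the protocol's sizing tests and assuming independence. Lymph-ICF should be restated for the F test, where the range is about 70–83% depending on the pattern of means.
2. **Fixed sequence, arm volume first.** Arm volume keeps 86%. The protocol should then state that confirmatory power for Lymph-ICF is about 69–73%, and that a Lymph-ICF benefit without an arm-volume benefit is supportive only.
3. **Both required.** No alpha adjustment is needed, but the stated power should be the joint power.

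Listing SF-36 under secondary endpoints would be a wording clarification only.

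The cost is one paragraph and somewhat lower stated power, with no added participants. The article reports 39 women randomized by September 2015 and places the primary analyses at the end of the randomized portion, so at that stage the rule could still be set in advance.

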**Discussion:**

The use of night-time compression as a self-management strategy for chronic breast cancer related lymphedema is seen as an innovative approach to improve long-term control over the condition. This trial aims to advance the knowledge on self-management strategies for lymphedema.

**Trial registration:**

This trial was registered at clinicaltrials.gov on July 9^th^, 2014 (NCT02187289)

## Background

Breast cancer is the most common cause of cancer in Canadian women with an estimated 25,000 developing the disease in 2015 [1]. With a current 5-year survival rate of 88 %, a substantial number of women in Canada are living with a history of breast cancer [1]. One of the more frequent complications following treatment for breast cancer is lymphedema, a significant swelling of the arm that occurs on the surgical side. Lymphedema is a lifelong condition that tends to worsen over time [2]. Recent data suggest that approximately 21 % of women who undergo treatment for their breast cancer are diagnosed with lymphedema [3]. Of these cases, approximately half will develop chronic progressive lymphedema [4, 5].

The impact of lymphedema on the breast cancer survivor is often profound, resulting in negative changes in self-image, increased anxiety, and poorer quality of life [6, 7]. Overtime, lymphedema can create considerable disability with recurrent infections in the limb, functional impairment, and pain [2, 8]. Many survivors see lymphedema as an ongoing reminder of cancer to themselves, friends, and family [6]. Compounding the problem is that survivors report receiving limited support and inadequate or conflicting information on the condition and its treatment from healthcare providers [6]. In a matched cohort analysis of breast cancer survivors with and without lymphedema, those with lymphedema had significantly higher medical costs at 2 years (range of $14,877 to $23,167) and were twice as likely to develop an infection in the limb as compared to survivors without lymphedema [8].

At present, there are no known curative treatments, either surgical or pharmacological, for lymphedema [9]. Rehabilitative treatments, also called conservative treatments, are prescribed to reduce and maintain limb size, to restore function, to reduce pain, and to improve the appearance of the limb [9, 10]. An initial intensive treatment program is usually prescribed to reduce the lymphedema (Phase I) and is followed by a maintenance phase (Phase II) which aims to promote life-long maintenance [11]. Decongestive Lymphatic Therapy (DLT) is a 2-to-4 week intensive treatment program comprised of daily manual lymph drainage (MLD) massage (a specialized massage technique), wrapping with multi-layered short-stretch compression bandages (worn 23 h per day), exercise, and education [12]. The current recommended intensive treatment approach for Phase I is DLT, with or without the inclusion of the MLD massage component [9]. Following treatment to reduce the swelling, a compression sleeve is prescribed. Compression sleeves represent current standard of care in lymphedema maintenance (Phase II) [9].

A prospective cohort study including 682 women with breast cancer related lymphedema examined the ability of women to maintain arm lymphedema volume following an intensive course of reduction treatment for lymphedema [13]. In the study, the authors observed a gradual increase in lymphedema volume over time among study participants, with the greatest increases seen in the first year. The risk of treatment failure, defined as a >50 % relapse in arm lymphedema volume from baseline levels, was 38.1 %, 53.1 %, and 64.8 % at 1, 2, and 4 years respectively [13]. Interestingly, women who wore a day-time compression sleeve and also wrapped their affected limbs with compression bandages (CB) at night (a minimum of 4 nights per week), had a significantly reduced risk of relapse in arm lymphedema volume [hazard ratio, 0.53, (0.34–0.82), *P* = 0.004] [13]. The authors concluded that successful control of lymphedema may be dependent on the combined use of the compression sleeve and CB during day and night periods, respectively.

Applying compression at night is an option that is usually presented to the survivor when the condition is advanced or when relapses in symptoms and/or arm lymphedema volume occur [9]. When night-time compression is indicated, the survivor is taught how to apply the bandages to the arm [Fig. 1]. Although many survivors are able to bandage their arm independently, a family member or significant other is often taught the bandaging technique and assists the survivor at night. Various types of night-time compression system garments (NCSGs) have been designed as alternatives to CB. NCSGs are simple to use, quick to apply to the limb, and can be easily adjusted to provide the appropriate amount of pressure. In general, these compression system garments apply gentle gradient pressure to the limb through a garment with a foam liner and a series of adjustable straps [Fig. 2]. The garments are non-elastic and provide low resting pressure on the limb, making them safe to wear while sleeping at night. NCSGs provide an alternative self-management strategy for women to reduce the time burden associated with compression bandaging as well as for those unable to appropriately apply CB to their arm (e.g., older individuals with mobility issues and/or those who live alone). Although NCSGs are already available for purchase, as with many marketed treatment options for lymphedema, little is known about their effectiveness.

**Fig. 1 Fig1:**
[figure not shown]
Compression bandaging

**Fig. 2 Fig2:**
[figure not shown]
Example of strapped version of a night-time compression system garment

### Hypotheses of randomized controlled trial (Phase I)

Standard care plus the addition of CB will provide statistically significant improved management of **arm lymphedema volume** compared to standard care alone at 12-weeks.Standard care plus the addition of NCSG will provide statistically significant improved management of **arm lymphedema volume** compared to standard care alone at 12-weeks.Standard care plus the addition of NCSG will provide statistically significant benefit in **quality of life**, **sleep and self**-**efficacy** over standard care plus CB and standard care alone at 12-weeks.

### Objectives

The primary objectives of the randomized controlled phase of the trial are to determine the effect of night-time compression on arm lymphedema volume maintenance and quality of life in breast cancer survivors who have completed intensive reduction treatment for their lymphedema. These questions are seen as valuable for informing implementation of night-time compression as a self-management strategy for lymphedema in the clinical setting. The primary objectives of follow-up are to evaluate the long-term adherence to use of night-time compression and the timing of the intervention effect. As well, this follow-up period will allow us to better understand who may benefit the most (or least) from the addition of night-time compression.

## Methods/Design

The study will be a parallel 3-arm, multi-centre randomized fast-track trial including the Cross Cancer Institute (CCI) in Edmonton, Tom Baker Cancer Centre (TBCC) in Calgary and Mount St. Joseph’s Hospital (MSJ) in Vancouver. Women enrolled in the study will be stratified by accruing centre (CCI, TBCC, MSJ) and by lymphedema severity (i.e., mild versus moderate lymphedema as per the classification criteria of International Society of Lymphology) [9, 14], and then randomly assigned to one of three groups: (1) standard care (day-time use of a compression sleeve alone); (2) standard care plus night-time compression by self-administered or assisted CB; (3) standard care plus night-time compression by a traditional NCSG. The duration of the primary intervention period will be 12 weeks. Results from the pilot study and previous case studies suggest a small initial reduction in arm lymphedema volume from administration of the traditional strapped NCSG over the first 6 weeks with stabilization of arm volume (plateau) occurring thereafter. Thus, the 12-week intervention period is deemed sufficient to observe an intervention effect and was chosen to align with current clinical follow-up time periods. Following the 12-week intervention period, participants in the CB and standard care groups will be measured for a NCSG. Participants in these two groups will follow the protocol as per the NCSG group during weeks 13 to 24 [Fig. 3].

